### Secondary Outcomes Analyses

For secondary outcomes, linear mixed-effects regression models, with the same predictors and covariates as the CLMM model will be used. Effect sizes will be estimated as Cohen d for mixed-effects models by dividing the unstandardized β coefficient for the time x treatment interaction by the baseline SD, with 95% bootstrap confidence intervals derived from 1000 simulations. Under the assumption that data are missing at random, mixed-effects regression analyses for repeated measures (including all assessment points), provide unbiased estimates and standard errors.^43^ This assumption indicates that, conditional on observed data, the probability of missingness depends only on observed variables and not on unobserved values.^44^ If >30% of the primary outcome data are missing at the primary end-point, we will conduct NMAR sensitivity analyses to assess the robustness of the results to departures from the MAR assumption. For CGI-I, the number of participants classified as responders will be presented. Treatment response is defined as a CGI-I rating of 1 (“very much improved”) or 2 (“much improved”).^15,45,46^ Differences between treatment groups in participant satisfaction and therapist time will be analyzed using independent samples t tests. To examine whether blinded assessors’ guesses of treatment allocation differ from chance, a t test will be conducted. All tests will be 2-sided, with statistical significance set at P < .05.

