## Secondary endpoint

Secondary endpoints are:

- 3 months after treatment.
- 1 years after treatment.
- 5 years after treatment.
- Distal outcomes will be examined after the participant’s 18th birthday using data from Swedish national registries retrieved 1 to 10 years after treatment completion, depending on age at study inclusion.
- Weekly during treatment.

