# Table 2. Information on the time points for completion and responders of measurements related to all hypotheses

|  | TRIAL PERIOD | | | | | | | | | | | | |
| --- | --- | --- | --- | --- | --- | --- | --- | --- | --- | --- | --- | --- | --- |
|  | Enrolment | Randomization | Post-randomization | | | | | | | | | | |
| Assessment point | Baseline | | 1w | 2w | 3w | 4w | 5w | 6w | POST | 3M | 12M | | 60M |
| **ENROLMENT** |  | |  |  |  |  |  |  |  |  |  | |  |
| Eligibility screen | X | |  |  |  |  |  |  |  |  |  | |  |
| Informed consent | X | |  |  |  |  |  |  |  |  |  | |  |
| Randomization | X | |  |  |  |  |  |  |  |  |  | |  |
| **TREATMENT**  POET  Supportive treatment |  | |  | | | | | |  | | | | |
| **ASSESSMENTS** |  | |  |  |  |  |  |  |  |  | |  |  |
| ***Clinician rated*** |  | |  |  |  |  |  |  |  |  | |  |  |
| MINI-KID | X | |  |  |  |  |  |  |  |  | |  |  |
| CGI-S | X | |  |  |  |  |  |  | X | X | | X | X |
| CGI-I |  | |  |  |  |  |  |  | X | X | | X | X |
| C-GAS | X | |  |  |  |  |  |  | X | X | | X | X |
| WSAS | X | |  |  |  |  |  |  | X | X | | X | X |
| RCADS-47 | X | |  |  |  |  |  |  | X | X | | X | X |
| CEQ | X | |  |  | X |  |  |  |  |  | |  |  |
| PIAS |  | |  |  | X |  |  |  | X |  | |  |  |
| ***Adolescent rated*** |  | |  |  |  |  |  |  |  |  | |  |  |
| RCADS-11 | X | | X | X | X | X | X | X | X | X | | X | X |
| PMERQ-short | X | |  |  |  |  |  |  | X | X | | X | X |
| Selected items from PMERQ-short |  | | X | X | X | X | X | X |  |  | |  |  |
| DERS-16 | X | |  |  |  |  |  |  | X | X | | X | X |
| Selected items from DERS-16 |  | | X | X | X | X | X | X |  |  | |  |  |
| ERQ-CA | X | |  |  |  |  |  |  | X | X | | X | X |
| Selected items from ERQ-CA |  | | X | X | X | X | X | X |  |  | |  |  |
| PAQ-S | X | |  |  |  |  |  |  |  | X | | X | X |
| DSHI-Y |  | |  |  |  |  |  |  | X | X | | X | X |
| PANAS | X | | X | X | X | X | X | X | X | X | | X | X |
| SEQ-C | X | | X | X | X | X | X | X | X | X | | X | X |
| BSL-23 | X | |  |  |  |  |  |  | X | X | | X | X |
| EBQ | X | |  |  |  |  |  |  | X | X | | X | X |
| CHU-9D | X | |  |  |  |  |  |  | X | X | | X | X |
| CSQ |  | |  |  |  |  |  |  | X |  | |  |  |
| Study specific questionnaire on Adverse events |  | |  |  |  |  |  |  | X |  | |  |  |
| CEQ | X | |  |  |  |  |  |  |  |  | |  |  |
| One selected item from CEQ |  | | X | X | X | X | X | X |  |  | |  |  |
| Single-item assessment of suicidal ideation and plans | X | | X | X | X | X | X | X | X | X | | X | X |

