### Analysis of Baseline Characteristics

Demographic and baseline characteristics will be summarized for each treatment group. In accordance with CONSORT 2025 recommendations, no significance testing of baseline differences will be performed.^41^ Data distributions and potential outliers will be visually inspected, and sensitivity analyses will be run without outliers. Categorical variables will be summarized as counts and percentages; ordinal and continuous variables as medians and interquartile ranges or means and standard deviations, as appropriate. Data will be analyzed according to the participants’ original treatment allocation in line with intention-to-treat principles, including all available data in all analyses, with no cases omitted.

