### Primary Outcome Analysis

To evaluate the primary outcome, change in CGI-S scores will be analyzed using a cumulative link mixed model (CLMM) implemented in the ordinal package in R (R Project for Statistical Computing).^42^ The model will include a random intercept for participant, a dummy-coded site variable, a dummy-coded time variable (before treatment, immediately after treatment, and 3 months after treatment, with before treatment as the reference category), the treatment condition, and the interaction between the time variable and treatment. Coefficients from the CLMM represent the log odds of being classified in a higher CGI-S category, these will be converted to odds ratios.

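### Read as written, the three-level time factor keeps the week 1–6 RCADS-11, PANAS and SEQ-C scores out of the models for the post-treatment and 3-month effects, contrary to the stated use of all assessment points

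*Protocol*

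**What the plan says.** Protocol, Primary Outcome Analysis: the CGI-S model has a random intercept for participant, site, treatment, the time-by-treatment interaction and "a dummy-coded time variable (before treatment, immediately after treatment, and 3 months after treatment, with before treatment as the reference category".

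Protocol, Secondary Outcomes Analyses: "linear mixed-effects regression models, with the same predictors and covariates as the CLMM model will be used". The section then justifies the handling of missing data: under missing at random, "mixed-effects regression analyses for repeated measures (including all assessment points), provide unbiased estimates and standard errors". Analysis of Baseline Characteristics adds a general promise of "including all available data in all analyses, with no cases omitted".

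Protocol, Table 2: the rows "RCADS-11 | X | | X | X | X | X | X | X | X | X" and "PANAS | X | | X | X | X | X | X | X | X | X" show collection at baseline, in each of weeks 1 to 6, immediately after treatment (POST) and at 3 months. SEQ-C has the same pattern. The Secondary endpoint section lists "Weekly during treatment" among the endpoints.

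Protocol, Mediation and moderation analyses: weekly change in emotion regulation is modelled as a mediator of effects on mental health symptoms, with SEQ as the competing mediator. PANAS is not named there.

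**The concern.** A three-level time factor suits CGI-S, which is not rated during treatment. Carried over to scales collected weekly, it leaves the week 1–6 scores with no level, so they cannot enter the model. The section nevertheless relies on all assessment points being included.

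What is at stake is the missing-at-random assumption. An adolescent who completes several weekly forms but neither the POST nor the 3-month form contributes only a baseline score to the three-level model. Missingness must then be ignorable given baseline and arm, although the course during treatment is on file. RCADS-11 is the adolescent's own report of anxiety and depression, which falls under Hypothesis 1.1. The planned sensitivity analysis for data not missing at random does not cover these scales, because its trigger is tied to the primary outcome.

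**Working it through.** **1. The plan's own figure.** Inputs from Power analysis, Secondary continuous outcomes: 194 per group, 10% attrition, ICC 0.5, d = 0.30, two-sided α = 0.05, two time points.
- SD of change = √(2 × (1 − 0.5)) = 1; n = 194 × 0.9 = 174.6 per arm.
- SE = √(2/174.6) = 0.107; power = Φ(0.30/0.107 − 1.96) = 80.0%.
- The random-intercept model that keeps the dropouts' baseline scores gives SE 0.1057 and power 81.0%.

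The stated power above 80% reproduces. It assumes two time points, so the weekly scores play no part in it.

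**2. Count from Table 2.** Per scale to 3 months: 1 baseline + 6 weekly + 1 POST + 1 at 3 months = 9 scores. Three have a time level and six do not. At N = 388 that is up to 388 × 6 = 2,328 of 388 × 9 = 3,492 scores per scale.

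**3. Precision.** Generalised least squares, ICC 0.5, d = 0.30 at POST. Dropouts are assumed to supply all six weekly scores and to miss both POST and 3 months.

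| Missing | SE, 3 levels | SE, 9 levels | Power, 3 levels | Power, 9 levels |
|---|---|---|---|---|
| 0% | 0.1015 | 0.1015 | 84.0% | 84.0% |
| 10% | 0.1057 | 0.1047 | 81.0% | 81.8% |
| 20% | 0.1106 | 0.1084 | 77.4% | 79.0% |
| 30% | 0.1167 | 0.1131 | 72.9% | 75.6% |

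The gain in precision is small.

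**4. Bias.** The documents give no dropout mechanism, so everything in this step is assumed. Scores are multivariate normal with correlation 0.45 + 0.4 × 0.85^lag, lag in weeks. This gives 0.58 between baseline and POST (lag 7) and 0.74 between week 5 and POST (lag 2). The true effect is 0.30. Dropout before POST is logistic in the week-5 score, with log-odds slopes per SD of 0.26, 0.5 and 1 (odds ratios 1.3, 1.65 and 2.7). With 10% missing, the estimated POST effect is:

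| Dependence of dropout on the score | 3 levels | With weekly scores |
|---|---|---|
| Equal in both arms | 0.30 | 0.30 |
| Control arm only, slopes 0.26 to 1 | 0.29 to 0.26 | 0.30 |
| Opposite directions by arm, slopes 0.5 to 1 | 0.26 to 0.23 | 0.30 |

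Reversing which arm loses its worse-scoring adolescents changes the sign of the bias. By symmetry the one-arm range becomes 0.31 to 0.34 and the opposite-direction range 0.34 to 0.37. A separate simulation (ICC 0.5 with equal correlations, dropout driven by the week-6 score with slope 1.5, about 11% missing) also shows inflation. Three levels give 0.34 with dependence in the POET arm only and 0.37 with opposite directions; nine levels give 0.31 in both.

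**5. Covariance.** With serially correlated scores, slope 1 and dropout before week 6 in opposite directions at 20% missing, three levels give 0.14, nine levels with only a random intercept 0.27, and nine levels with the true covariance 0.29. The weekly levels remove most of the bias and a richer covariance removes most of the rest.

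**The case against.** The strongest reply is that the sentence on predictors is a template. Table 2 gives PAQ-S no POST score, several parent scales no POST score and DSHI-Y no baseline, so the three levels cannot apply literally to every secondary outcome. The long-term section also carries the same method to 1 and 5 years, which have no level in the CGI-S model. On that reading time follows each outcome's schedule and nothing is contradicted. This shows that the authors may intend the right model. It does not remove the problem, because the only time coding written down has three levels and no sentence says that it varies by outcome.

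A second reply is that weekly scores are meant for mediation, since Hypotheses 1.1 and 2.1 concern only POST and 3 months. This stands in part. A reader might infer that the weekly data are discarded altogether; the mediation section contradicts that for SEQ and probably for the weekly symptom scores. PANAS has no named weekly analysis, and the mediation model does not replace the models for the POST and 3-month effects.

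A third reply is that time coding can be left to the SAP. That would hold if the protocol were silent, but it fixes a rule that conflicts with its own justification.

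It is also fair that mild dependence matters little: a bias of 0.01 is about a tenth of the SE of 0.1057. Adolescents who disengage may skip the weekly forms too, which would reduce the benefit of including them.

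**Conclusion.** The point holds as a conflict between the written model and its stated basis, limited to three adolescent-rated scales. Six of nine scores to 3 months on each have no place in the models for the POST and 3-month effects.

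The bias is a possibility under assumptions, not a forecast. It requires dropout before POST that depends on weekly scores differently by arm. At 10% missing and slopes up to 1 per SD, the illustrative downward cases run from 0.29 to 0.23 against a true 0.30. The largest shift, 0.07, is about two thirds of an SE (0.07/0.1057 = 0.66). The direction cannot be known from the documents. With equal dependence in both arms there is no bias.

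Two stronger conclusions are tempting and unsupported: that the trial's main result is at risk, and that the secondary outcomes are underpowered. CGI-S is not measured weekly, and the stated power reproduces without the weekly scores.

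**What to change.** In Secondary Outcomes Analyses, state that the time factor follows each outcome's Table 2 schedule. For RCADS-11, PANAS and SEQ-C its levels are then baseline, weeks 1 to 6, POST and 3 months, each post-baseline level with its treatment interaction, and with an unstructured or serially correlated within-person covariance in place of a random intercept alone. Keep the POST and 3-month contrasts as the reported effects. Outcomes collected only at baseline, POST and 3 months keep the three levels.

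The cost is a sentence or two and a slightly larger model: nine visits, or 9 × 10/2 = 45 covariance parameters if unstructured, for 388 participants. The time factor will differ between outcomes. No new data are needed.

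If the weekly scores are meant for mediation only, the protocol should say so and narrow its statement on all assessment points. That removes the conflict in wording but leaves the stronger missing-at-random assumption in place.

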# Outcome measures

## Primary Outcome Measure

**Clinician rated clinical global symptom severity** will be measured with The Clinical Global Impressions-Severity (CGI-S).^19^The CGI-S is an ordinal scale ranging from 1 to 7, with higher scores indicating greater severity. CGI-S is administered by a blinded assessor before randomization and at immediately after treatment (primary endpoint), 3 months after treatment, and at 1 and 5 years follow.

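### The missing-at-random claim covers more than the primary CLMM conditions on: dropout tied to weekly symptoms can bias the primary odds ratio if that tie differs by arm, and nothing planned would show it at about 10% attrition

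*Protocol*

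**What the plan says.** **Primary model.** Protocol, Primary Outcome Analysis: "The model will include a random intercept for participant, a dummy-coded site variable, a dummy-coded time variable". Treatment and the time-by-treatment interaction complete the list. The time variable covers baseline, post-treatment and 3 months.

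**Secondary models.** These are linear mixed models "with the same predictors and covariates as the CLMM model will be used".

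**Missing data.** Protocol, Secondary Outcomes Analyses: "Under the assumption that data are missing at random, mixed-effects regression analyses for repeated measures (including all assessment points), provide unbiased estimates". The next sentence explains the assumption: "This assumption indicates that, conditional on observed data, the probability of missingness depends only on observed variables and not on unobserved values". One sensitivity analysis is tied to missing data: "If >30% of the primary outcome data are missing at the primary end-point, we will conduct NMAR sensitivity analyses". This text stands under the secondary outcomes, but the 30% rule names the primary outcome, so it governs that analysis too.

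**What is measured when.** Protocol, Primary Outcome Measure: "CGI-S is administered by a blinded assessor before randomization and at immediately after treatment (primary endpoint", then at 3 months, 1 year and 5 years. There is no CGI-S between baseline and post-treatment. Table 2 schedules RCADS-11, PANAS and SEQ-C at each of weeks 1 to 6. The only analysis stated for weekly data is the mediation model (Mediation and moderation analyses).

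**Planned attrition.** Protocol, Power analysis: about 10%, with 388 randomized to leave 350.

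**The concern.** A likelihood analysis may ignore the missingness process only if, given the data in that likelihood, missingness does not depend on the missing values. Here those data are arm, site, visit and observed CGI-S. For an adolescent with no post-baseline interview, the model sees one baseline CGI-S score.

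Suppose adolescents whose weekly symptoms worsen are more likely to miss the post-treatment interview. Missingness then depends on an observed variable, so it fits the protocol's wording of MAR. But the variable is outside the model and also predicts the missing CGI-S, so the unbiasedness claim does not carry over to this model.

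The protocol makes such loss plausible. Therapists review weekly self-ratings for deterioration, and families with acute problems are helped to obtain other care (Measures to minimize risks for participants). Those who discontinue are followed by clinic routine (Withdrawal criteria). Feeling that treatment is not helping is a listed expected event (Assessment of expected AE). Participants and therapists know the allocation (Blinding).

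At stake is the size of the primary odds ratio and, in some patterns, its type I error.

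**Working it through.** **1. The plan's own figures.** 350 / (1 − 0.10) = 388.9 and 388 × 0.90 = 349.2, so N = 388 agrees with the stated attrition. The target is ln(2.2) = 0.788 on the log-odds scale.

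**2. Assumed inputs.** The documents give neither the pilot thresholds, nor the correlation of weekly scores with CGI-S, nor any dropout mechanism. These were assumed and varied. Data were simulated for baseline, post-treatment and 3 months with a true odds ratio of 2.2, and the random-intercept cumulative logit model was fitted by Gauss-Hermite quadrature to 100,000 to 600,000 participants, so that bias is not confused with sampling error.

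- Set A: ICC 0.5; last weekly score correlated 0.57 with post-treatment CGI-S; dropout odds × 2.7 per SD of that score in one arm and flat in the other.
- Set B: random-intercept SD 1.48 (ICC 0.40); weekly score correlated 0.5 or 0.7 with latent post-treatment severity; several dropout patterns.
- Set C: as a stress case, weekly-score correlation 0.8.

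Except where stated, dropouts miss both post-treatment and 3 months. Each arm is calibrated to the same missing rate, except under the common rule, where arm rates follow from the rule.

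**3. Fitted odds ratio by dropout pattern.**

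| Pattern (set) | Full data | 10% missing | 20% missing | 30% missing |
|---|---|---|---|---|
| Same rate and slope in both arms (B) | 2.26 | 2.26–2.28 | 2.24–2.29 | 2.26–2.27 |
| One common rule for all (B) | 2.20 | 2.11–2.19 | 2.06–2.18 | 2.02–2.16 |
| Control leaves when worse, POET unrelated (A) | 2.2 | about 2.0 | about 1.8 | about 1.7 |
| Control leaves when worse, POET unrelated (B) | 2.26 | 2.00–2.08 | 1.80–1.91 | 1.63–1.79 |
| POET leaves when worse, control unrelated (A) | 2.2 | about 2.5 | about 2.7 | about 3.0 |
| POET leaves when better, control when worse (B) | 2.26 | 1.79–1.90 | 1.43–1.61 | 1.16–1.42 |

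In set C, dropout tied to symptoms in one arm only gave about 1.9 or 2.6 at 10% missing.

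**4. What this means at 10% missing.** In set A the bias toward the null is 0.10 in log odds ratio, and the standard error of the interaction at n = 349 is 0.29.

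- Power without bias: Φ(0.788/0.29 − 1.96) = Φ(0.76) = 0.78.
- Power with bias: Φ((0.788 − 0.10)/0.29 − 1.96) = Φ(0.41) = 0.66.
- Type I error with a shift of 0.10/0.29 = 0.34 standard errors: 1 − Φ(1.62) + Φ(−2.30) = 0.053 + 0.011 = 0.064.

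Simulated type I error in set A was about 6.4%, 10–11% and 17% at 10%, 20% and 30% missing. With half the dependence it was 5.5–8.6% over the same range.

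**5. Does the 3-month visit rescue the model?** Hardly. In set B, with control leaving when worse and 10% missing, the odds ratio was 2.09 or 2.01 when only post-treatment was missing, against 2.08 or 2.00 when both visits were. In set C, observing half of the dropouts at 3 months barely helped.

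**6. Does the weekly score help?** Imputing CGI-S within arm from baseline CGI-S and the weekly score gave 2.21–2.28 in set B (not run for the common rule) and left a bias of at most 0.009 in set A. This flatters the remedy, because the imputation used the very score that generated dropout.

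**The case against.** **It belongs in the statistical analysis plan.** Imputation models and auxiliary variables usually sit there, and that document is not at hand. This stands for the detail of any imputation. It does not dispose of the point, because the protocol itself fixes the model's terms, claims unbiasedness and sets the 30% threshold.

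**The MAR sentence is not wrong.** It is a standard definition, and the claim is worded conditionally. That stands. A reader might infer that the protocol misdefines MAR; it does not. The weak step is from observed variables in general to a model that holds few of them.

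**Bias is not shown.** A reader might infer that symptom-driven dropout necessarily biases the primary odds ratio. The documents do not support this: nothing in them says that the dropout process differs by arm, and the arms share format, session weeks, therapists and weekly contact. With the same process in both arms there is essentially no bias. Under one common rule the largest loss at 10% missing is from 2.20 to 2.11, about 4%. This objection stands and limits the point to a possible bias.

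**Leaving treatment is not missing the interview.** Analysis is by intention to treat and post-treatment assessments are reimbursed, so interview loss may be low. That is fair, but the figures above refer to missing CGI-S, and the plan itself allows for about 10%.

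**The NMAR analyses could cover it.** Dropout through an omitted predictor is a departure from MAR for the fitted model, so those analyses might address it. But they run only above 30% missing.

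**Conclusion.** The point holds in conditional form. The primary model's MAR condition is narrower than the protocol's wording suggests, and the weekly symptom scores that could narrow the gap have no stated role in handling missing CGI-S.

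The primary odds ratio can be biased if the relation of symptoms to dropout differs by arm. At 10% missing, with dependence in one arm only, 2.2 becomes about 1.9–2.1 or 2.5–2.6; opposite dependence in the two arms gave 1.79–1.90 against 2.26. Direction depends on the pattern. With the same process in both arms the bias is near nil.

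All these sizes rest on assumed correlations, dropout slopes and thresholds. They show what is possible, not what is expected. The larger type I error figures need two to three times the planned attrition.

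The firmest part needs no simulation: at the expected attrition the plan contains no missing-data sensitivity analysis that could reveal the problem.

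**What to change.** 1. Keep the cumulative link mixed model as the main analysis.
2. In Secondary Outcomes Analyses, state that MAR is assumed conditional on the variables in the model (arm, site, visit and observed outcome), and limit the unbiasedness claim to that.
3. Pre-specify one companion analysis, run whatever the missing rate. Multiply impute missing post-treatment and 3-month CGI-S separately by arm from baseline CGI-S and a compact summary of weekly RCADS-11, for example the last available score. Refit the same model to each completed data set and pool.
4. Keep the imputation model small. RCADS-11, two PANAS subscales and SEQ-C over six weeks would be 4 × 6 = 24 correlated predictors for about 175 observed outcomes per arm, which risks instability with sparse CGI-S categories.

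Cost: protocol wording, modest programming and some Monte Carlo noise; no new data. Early leavers may lack late weekly scores, so the companion analysis reduces the problem but does not remove it. It should be fixed before outcome data are seen.

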### Withdrawal criteria

Subjects can discontinue their participation in the trial at any time without any consequence to his/her continued treatment. If the subject discontinues the trial, follow-up of this subject will be performed according to the clinic’s routine.

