# Methods: Assignment of interventions

## Randomization

Eligible participants will be randomly assigned (1:1) to either the POET intervention or the Supportive Treatment condition. Randomization will be conducted in blocks of four or six within each participating Region. An independent researcher, not involved in participant recruitment or treatment delivery, will perform the randomization using an online system (Sealed Envelope Ltd) that employs a secure pseudo-random number generator.

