## Statistical methods

### Power analysis

#### Primary outcome

A simulation-based power analysis was performed. Based on the data from the pilot study)^15^, a simpler model without random effects was fitted to estimate the effect of time and the thresholds. Data was then generated using these values, and parameters that were varied, namely sample size, interaction between time and treatment (log-odds), and the variance of the random effect. Sample size took the values of 250, 300, 350, and 400, the interaction effect took the values of 0.59, 0.69, 0.79, and 0.88 (corresponding to ORs of 1.8, 2.0, 2.2, and 2.4), and the variance of the random effect took the values of 1.48 and 2.22 (corresponding to ICC of 0.4 and 0.6). For each combination of parameters, 700 datasets were simulated, and a cumulative link mixed model (CLMM) was fitted to the data. The p-value of the interaction effect was saved for each simulation, and power was calculated as the proportion of p-values less than 0.05. The CLMM model fitted in each iteration included a random intercept for participant, a dummy-coded time variable (before treatment, after treatment), the treatment condition, and the interaction between the time variable and treatment. The results from the power analysis are shown in Figure 2.

We concluded that 350 participants would give us >80% power to detect an interaction between treatment and time with an OR of 2.2. To allow for ~10% attrition, we set N to 388 participants.

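### The missing-at-random assumption behind the primary result is checked only if more than 30% of endpoint ratings are missing, three times the planned attrition and pooled over arms

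*Protocol*

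**What the plan says.** The missing-data rule stands in the protocol under Secondary Outcomes Analyses, but it concerns the primary outcome. The mixed models are justified there as follows: "Under the assumption that data are missing at random, mixed-effects regression analyses for repeated measures" are said to give unbiased estimates and standard errors. Then comes the condition: "If >30% of the primary outcome data are missing at the primary end-point, we will conduct NMAR sensitivity analyses".

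The sample size under Power analysis, Primary outcome, assumes far less loss: "To allow for ~10% attrition, we set N to 388 participants". The power statement for the secondary continuous outcomes also uses 10%.

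No other part of the protocol examines departures from MAR. Under Analysis of Baseline Characteristics, sensitivity analyses are planned without outliers. The sensitivity and scenario analyses under Health economic evaluation concern costs and QALYs.

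The Primary Outcome Analysis is a cumulative link mixed model (CLMM) for CGI-S at baseline, immediately after treatment and 3 months, with site, arm, time, the time-by-arm interaction and a random intercept. Table 2 shows CGI-S at baseline, POST and the follow-ups only, while RCADS-11 and PANAS are collected weekly during treatment. For a person who discontinues the trial, "follow-up of this subject will be performed according to the" clinic's routine.

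**The concern.** MAR cannot be tested from the observed data, and a low percentage of missing values does not make it true. How much a departure matters depends on the size of the effect, the fraction missing and how the loss is split between arms. The trigger looks only at the pooled fraction.

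The primary model has little to condition on for some participants. Someone with neither a POST nor a 3-month rating contributes only a baseline CGI-S row. The CLMM cannot use the weekly symptom scores given before that person was lost, although those scores are the best information on how treatment was going.

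At stake is whether a significant primary result could be reported with no evidence on how it depends on the unobserved ratings. An SAP that is not shown does not remove the point, because the protocol itself fixes the numeric rule.

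**Working it through.** **Inputs from the protocol.** N = 388, 194 per arm ("Eligible participants will be randomly assigned (1:1"). Attrition about 10%. Design statement: "We concluded that 350 participants would give us >80% power to detect an interaction between treatment and time with an OR of 2.2". Test level: "All tests will be 2-sided, with statistical significance set at P < .05".

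**The plan's own figure.** 350 / (1 − 0.10) = 388.9, that is 389 against the stated 388. Since 1 − 350/388 = 9.8%, the stated number agrees with about 10% attrition.

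**The trigger.** 30% / 10% = 3.0. In numbers, 0.30 × 388 = 116.4, so 116 missing ratings do not set it off. With equal arms, 40% missing in one and 19% in the other gives (40 + 19)/2 = 29.5% overall, also below the trigger.

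**Standard error (approximation).** The pilot thresholds and time effect behind the power simulation are not given, so I bracket the standard error (SE) of the log odds ratio at 350 evaluable participants.

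- From 80% power at OR 2.2: ln(2.2) / (1.960 + 0.842) = 0.7885 / 2.802 = 0.281.
- From a re-simulated two-time-point CLMM with assumed thresholds (700 datasets per setting, power 0.77 to 0.78): about 0.29. I use 0.288 = 0.7885 / 2.736, which corresponds to power 0.78.

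One side remark: the protocol says that "the variance of the random effect took the values of 1.48 and 2.22 (corresponding to ICC of 0.4 and 0.6"). On the logistic scale these values give ICCs of 0.4 and 0.6 only if read as standard deviations; as variances they give 0.31 and 0.40. Simulated power hardly moved between settings, so this does not affect the present point.

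**Scenario (assumption).** A fraction m is missing, equal in both arms. The analysis under MAR gives the observed OR. Missing POET participants are then assumed to have no benefit over control. To a first approximation:

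- SE(m) = SE(350) × √(350 / (388(1 − m)))
- adjusted log OR = (1 − m) × observed log OR
- z = adjusted log OR / SE(m)

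Odds ratios are expressed in favour of POET. In each pair of p values, the first uses SE 0.281 and the second 0.288.

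| Observed OR | Missing | p under MAR | Adjusted OR | p adjusted |
| --- | --- | --- | --- | --- |
| 2.2 | 10% | 0.005 / 0.006 | 2.03 | 0.012 / 0.014 |
| 2.2 | 20% | 0.008 / 0.010 | 1.88 | 0.035 / 0.039 |
| 2.2 | 25% | 0.011 / 0.012 | 1.81 | 0.055 / 0.061 |
| 2.2 | 30% | 0.014 / 0.016 | 1.74 | 0.084 / 0.091 |
| 1.8 | 10% | 0.037 / 0.041 | 1.70 | 0.060 / 0.067 |

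Worked line for OR 2.2 at 25%: SE = 0.281 × √(350/291) = 0.309; 0.75 × 0.7885 = 0.591; z = 0.591 / 0.309 = 1.92; p = 0.055.

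**Where significance is lost at OR 2.2.** Setting z = 1.96 gives m = 23.9% with SE 0.281 and 22.7% with SE 0.288. Both are below 30%. OR 1.8 is the smallest effect in the protocol's own simulation grid.

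**How large a departure is needed (SE 0.281, observed OR 2.2).** If δ is the log-odds penalty applied to missing POET participants only, significance is lost at δ = (0.7885 − 1.96 × SE(m)) / m.

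- 10% missing: δ = 2.36 (OR about 10.6)
- 20%: δ = 1.01 (OR about 2.8)
- 25%: δ = 0.73 (OR about 2.1)
- 30%: δ = 0.54 (OR about 1.7)

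Bringing the estimate down to no effect needs δ = 0.7885 / m: 2.63 at 30% (OR about 14) and 7.9 at 10%.

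**The case against.** The strongest reply is that the trial is planned for about 10% loss, and there a result at the design effect survives the no-benefit assumption comfortably. For such a result the exposed range is roughly 23 to 30% missing, more than twice the planned attrition, and nothing in the protocol predicts loss that high. This stands. It does not cover smaller effects: at OR 1.8 the planned 10% is enough to lose significance.

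Several stronger readings are tempting, but the document does not support them.

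- A reader might infer that the conclusion could reverse. It does not: in every scenario above the odds ratio still favours POET, and a change of sign would need a penalty too large to be plausible.
- A reader might infer that everyone missing at POST contributes only a baseline row. The model also includes the 3-month rating, so this holds only for those missing both.
- A reader might take the withdrawal rule to mean that people who stop the modules are no longer assessed. It covers people who discontinue the trial. The protocol also commits to using all available data by original allocation and pays adolescents for each completed post-treatment assessment.
- A reader might call outcome rating unblinded. Participants and therapists know the allocation, but CGI-S is rated by a blinded assessor.
- A reader might assume more dropout under POET because of its homework. That is possible, but the control arm also has weekly homework and no figure is given.

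The calculation is also one scenario. It penalises POET only; worse outcomes among missing control participants would push the other way. Scaling the log odds ratio by 1 − m is an approximation in a conditional ordinal model. Finally, the details of an imputation model can properly be left to an SAP. The point here is the threshold that the protocol itself sets.

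**Conclusion.** The concern holds in a limited form. The protocol fixes a rule that leaves MAR unexamined up to 30% missing, three times the planned attrition, and that cannot see imbalance between arms. If missing POET participants have no benefit over control, and the standard error at 350 evaluable participants is 0.28 to 0.29, a result at OR 2.2 is robust at 10% and 20% missing and loses significance from about 23 to 24%. A result at OR 1.8 loses it at the planned 10%. What is lost is statistical significance, not the direction of effect. Since the pilot parameters are not given, these figures show the order of magnitude and are not exact. The rule should be changed, but it does not invalidate the primary analysis.

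**What to change.** Under Secondary Outcomes Analyses, delete the 30% condition. State instead that, whatever the amount of missing data, CGI-S at the primary endpoint will be subjected to a delta-adjusted or reference-based sensitivity analysis with penalties varied separately by arm and the tipping point reported. Allow the weekly measures already collected, such as RCADS-11, to enter as auxiliary variables, so that information from participants with only a baseline CGI-S row is used. Place the statement under Primary Outcome Analysis, where the reader will look for it, and settle it before unblinded outcome data are seen.

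The cost is a change of wording and some extra analysis work. No new data, visits or participants are needed, and the primary CLMM stays as it is.
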